## Abstract

**Background:** Clinical practice guidelines (CPGs) have been developed with the aim of helping health professionals, patients, and caregivers make decisions about their health care, using the best available evidence. In many cases, incorporation of these recommendations into clinical practice also implies a need for changes in routine clinical practice. Using educational games as a strategy for implementing recommendations among health professionals has been demonstrated to be effective in some studies; however, evidence is still scarce. The primary objective of this study is to assess the effectiveness of a teaching strategy for the implementation of CPGs using educational games (e-learning EDUCAGUIA) to improve knowledge and skills related to clinical decision-making by residents in family medicine. The primary objective will be evaluated at 1 and 6 months after the intervention. The secondary objectives are to identify barriers and facilitators for the use of guidelines by residents of family medicine and to describe the educational strategies used by Spanish teaching units of family and community medicine to encourage implementation of CPGs.

(Continued on next page)

\* Correspondence: [contact]

Unidad de Apoyo a la Investigación, Gerencia Asistencial de Atención Primaria, Servicio Madrileño de Salud, [name]

Área Medicina Preventiva y Salud Pública, Facultad de Ciencias de la Salud, Universidad Rey Juan Carlos, Madrid, Spain

Full list of author information is available at the end of the article

(Continued from previous page)

**Methods/design:** We propose a multicenter clinical trial with randomized allocation by clusters of family and community medicine teaching units in Spain. The sample size will be 394 residents (197 in each group), with the teaching units as the randomization unit and the residents comprising the analysis unit. For the intervention, both groups will receive an initial 1-h session on clinical practice guideline use and the usual dissemination strategy by e-mail. The intervention group (e-learning EDUCAGUIA) strategy will consist of educational games with hypothetical clinical scenarios in a virtual environment.

The primary outcome will be the score obtained by the residents on evaluation questionnaires for each clinical practice guideline. Other included variables will be the sociodemographic and training variables of the residents and the teaching unit characteristics. The statistical analysis will consist of a descriptive analysis of variables and a baseline comparison of both groups. For the primary outcome analysis, an average score comparison of hypothetical scenario questionnaires between the EDUCAGUIA intervention group and the control group will be performed at 1 and 6 months post-intervention, using 95 % confidence intervals. A linear multilevel regression will be used to adjust the model.

**Discussion:** The identification of effective teaching strategies will facilitate the incorporation of available knowledge into clinical practice that could eventually improve patient outcomes. The inclusion of information technologies as teaching tools permits greater learning autonomy and allows deeper instructor participation in the monitoring and supervision of residents. The long-term impact of this strategy is unknown; however, because it is aimed at professionals undergoing training and it addresses prevalent health problems, a small effect can be of great relevance.

**Trial registration:** ClinicalTrials.gov: NCT02210442.

**Keywords:** Health personnel/education, Professional competence, Games, Experimental, Problem solving, Practice guidelines as a topic

## Background

Clinical practice guidelines (CPGs) are a set of “systematically developed statements to assist practitioner and patient decisions about appropriate health care for specific clinical circumstances” [1]. CPGs are developed with the aim of helping health professionals, patients, and caregivers make decisions about their health care, using the best available evidence. Several studies have proven that following the recommendations of certain CPGs improves patients’ health outcomes [2, 3]. In Spain, the National Health System Quality Plan of the Spanish Ministry of Health and Social Policy (GuiaSalud) has developed high-quality CPGs and made them available to all health professionals; these guidelines demonstrate great teaching potential that could improve health care. Many of these CPGs specifically target primary care health professionals [4].

Greater publication and dissemination of a CPG does not necessarily result in its systematic use. In many cases, incorporation of the CPG recommendations into clinical practice also implies a need for changes in routine clinical practice [5, 6]; thus, a subsequent implementation stage must be planned. Implementing a CPG involves launching a process aimed at the successful understanding and application of set recommendations through the use of effective communication strategies to promote change. This process constitutes one of the

basic phases of creating a CPG and requires a planning stage, in which special attention must be given to the context—both institutional and social—and the identification of barriers and facilitators that will determine later use of the CPG [5]. Several studies [7–9] have assessed factors that could influence implementation of evidence-based CPGs as well as selection of the best implementation strategies. CPGs are considered excellent teaching tools for acquiring skills and assessing clinical practice [10–12]. They provide information on the usefulness of diagnostic tests and their application in clinical practice. The important role played by CPGs in enabling resident doctors to prescribe appropriately and to identify potential conflicts of interest must be highlighted [13]. The educational program for family and community medicine was the first in Spain to incorporate CPGs as tools to enable the acquisition of essential competencies. In this program, understanding the conceptual basis of clinical practice is considered the first priority (i.e., an essential competence must be acquired by all residents, whose absence would result in doubt about the resident’s aptitude) [14], along with knowledge of evidence-based medicine (EBM) as a tool for clinical management through the use of CPGs, focusing on the patient.

There is evidence of limited CPG use by both residents and their mentors [15]. Several studies have confirmed the limited use of CPGs by resident doctors in various

areas, such as the prescription of antibiotics, preventive health activities, or handling prevalent pathologies such as hypertension or diabetes. A study evaluating antibiotic prescription in the treatment of urinary tract infections by family medicine residents at the Mayo Clinic found that only 30 % of prescriptions had been prescribed in accordance with the recommendations provided in the corresponding CPG [16]. Another study used a sample of 376 residents and explored how to approach renal failure treatment using a CPG that contained hypothetical clinical scenarios. The authors reported a significant lack of knowledge of the relevant risk factors, with the exception of hypertension [17]. In addition, the majority of the 127 residents included in a study assessing subjects' knowledge regarding screening for colon cancer reported family history of colorectal cancer as a screening factor; however, their knowledge regarding screening recommendations in cases of familial colon polyposis was limited [18]. The effectiveness of the different strategies aimed at increasing adherence to CPG recommendations has previously been evaluated, and most have been shown to improve adherence; the implementation of educational programs, mostly as part of more complex interventions, has also been shown to improve outcomes [19–21]. Some of these strategies specifically targeted resident doctors [17].

The teaching potential of educational games in stimulating learning and individuals' ability to analyze, synthesize, and evaluate information has been widely studied [22]. In previous years, we have witnessed the incorporation of games as virtual educational tools for supporting the training of students and resident doctors [23, 24]. The inclusion of educational games as a strategy for implementing recommendations among health professionals and resident doctors counts on broad acceptance and helps students acquire new knowledge and abilities, in addition to improving attitudes in an interactive, playful way, thus improving adherence to recommendations [25, 26]. A Cochrane collaboration review concluded that there was no evidence supporting the effectiveness of educational games in the training of health professionals, and given their potential, it seems necessary to perform quality research on the impact of these games on health professional training. Research must include the evaluation of results regarding professional performance, decision-making, the clinical care process, and, if possible, patient outcomes [27, 28].

Our proposal regarding educational games [29] focuses on the guidelines approved by the National Health System Quality Plan of the Spanish Ministry of Health and Social Policy. The selection criteria of guidelines include their applicability to severe or chronic, highly prevalent pathologies in primary health care that are included in the relevant areas within which residents must acquire

competencies. Several members of this trial's research team have been part of the working groups that developed these guidelines and have participated in their subsequent dissemination and implementation [30].

Teaching strategies that improve resident doctors' application of the CPG recommendations could have a direct impact on the improvement of health care. This impact would be particularly significant in the case of family medicine residents because more than 40 % of doctors who start their residency in Spain will train as family medicine doctors. These professionals will address the health problems of more than 90 % of the population; hence, any effective intervention in this group could have a significant effect.

### Hypothesis

A teaching strategy based on the incorporation of educational games for the implementation of CPGs, compared with the usual dissemination strategy, will improve knowledge and abilities related to clinical decision-making by residents in family medicine. A difference of at least 10 points between the EDUCAGUIA intervention group and the control group in the evaluation questionnaires will be considered statistically significant.

### Objectives

#### Primary

The primary objective of this study is to assess the effectiveness of a teaching strategy for the implementation of CPGs using educational games (e-learning EDUCAGUIA) to improve knowledge and abilities related to clinical decision-making by residents in family medicine, in contrast with typical CPG dissemination. The primary outcome will be evaluated at 1 and 6 months after the intervention.

#### Secondary

1. To describe the adherence to educational games and their acceptance by resident doctors
2. To describe the educational strategies used by Spanish family and community medicine teaching units to encourage CPG implementation
3. To identify barriers and facilitators for the use of CPGs by residents in family medicine

### Methods/design

#### Design

A multicenter clinical trial with randomized allocation by clusters.

Phase I will consist of a survey collected from family medicine residency program directors in Spain, the development of the educational games interface, and the elaboration of the competence tests.

Phase II will comprise a qualitative study to identify barriers and facilitators to the guideline implementation (Fig. 1).

### Setting

Teaching units of family and community medicine (TUFCM) in Spain.

### Study population

1. Teaching units of family and community medicine inclusion criteria
  - a. Legal criteria: having Spanish Ministry of Health approval for family medicine teaching to resident doctors and nurses
  - b. Residency program director agreement for trial participation
2. Family medicine residents' inclusion criteria
  - c. Third- and fourth-year residents belonging to teaching units of family and community medicine
  - d. Not opposed to participation

### Recruitment

All Spanish teaching units will be contacted by mail offering participation via an agreement form to participate in the EDUCAGUIA study. TUFCM agreeing to participate to the study will be randomly assigned to one of the two groups: the intervention or the control group.

### Sample size

The sample size has been calculated considering a relevant post-intervention average difference of 10 points on a 100-point evaluation questionnaire between groups and a standard deviation of 0.5 [31]. Assuming an alpha error of 0.05 and a beta error of 0.10, 84 subjects are required for each group. Because randomization is performed by clusters, the sample size has been adjusted to take into account the design effect. Thus, for an average of 30 residents per teaching unit, and an intraclass correlation coefficient (ICC) of 0.03 (literature shows an ICC of 0–0.052 for similar teaching interventions) [32], a design effect of 1.87 has been obtained. With these assumptions, and expecting a 25 % loss to follow-up after a 6-month period, the required sample size is 394 (197 per group).

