### Randomization

Allocation will be performed by clusters, and the randomizing unit will be the teaching units. The analysis unit will be the residents. Randomization will be performed by using the Epidat 4.1 software module to assign patients' treatments. The intervention "e-learning EDUCAGUIA" will be regarded as the treatment, and the routine CPG dissemination system will be used as a control variable. To obtain the same number of centers

in both the intervention and control groups, the option of balanced groups will be chosen.

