**Statistical analysis**

1. Descriptive and exploratory analysis: This analysis will include participants' baseline characteristics and outcomes, means and standard deviations (SD) for

continuous variables, and proportions for categorical variables with its corresponding 95 % confidence interval (CI). Baseline comparison between the two groups in terms of the score competence test and descriptive and prognostic factors will be performed by bi-variant statistical tests.

2. Inferential analysis: Student's *t* test with a 95 % CI will be performed to compare both groups' results in the competence test in terms of score at baseline and 1- and 6-month post-implementation of each CPG recommendation.
3. Multilevel analysis: a mixed model will be constructed for the evaluation of the influence of the teaching unit on the effectiveness of the intervention. The dependent variable will be the score obtained in the competence test. The model will consist of two levels: resident doctors will comprise the first level and the teaching unit will comprise the second.
4. Dropouts and missing data

Because this trial will use an online system to allocate participants and collect baseline and outcome data, participants can leave the study at any time. To minimize the possibility of dropouts and missing data, several strategies will be considered. If a participant leaves the study before randomization, the participant will be excluded and we will not consider this as missing participant data.

All statistical tests will be performed with an intention-to-treat analysis. The last observation carried forward will be used for missing data imputation, and there will be report analyses with and without imputation [36].

Significance will be set at  $p < .05$ . Calculations will be performed using MLwiN and STATA v.12 software with specific related modules.

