### Discussion

Teaching units from across Spain will participate in this clinical trial, which anticipates high external outcome validity. Additionally, this intervention might provide information to consider for training in other specialties.

The intervention to be assessed cannot be masked, which could influence its effect. Because there is a possibility of contamination bias among residents, randomization by clusters has been proposed, under the assumption that the number of clusters will be sufficient for each group. Geographic dispersion of the teaching units reduces the possibility of contamination.

Teaching strategies are complex interventions; the design of educational games as an interactive, self-learning application allows for standardization of the intervention.

The considerable variability foreseen between teaching units regarding training in CPGs could imply that some residents have better training with some of these CPGs, which could result in a lack of improvement in these residents' decision-making scores (competency test score). However, this possibility will be adjusted using the training variables of both the teaching units and the residents.

To evaluate the intervention's effectiveness, the primary measurement will take place 1 month after implementation; at this time, our primary objective will be to confirm the effectiveness of the e-learning EDUCAGUIA strategy as a learning tool. Its effect at 6 months after the intervention might not remain, which would lead to a study on the effectiveness of reinforcement interventions. Measuring the primary response at 6 months was considered an option, but the characteristics of training during residency periods make it possible for the residents to acquire the knowledge and abilities of the intervention during rotations or other courses within that time period, thus hindering the isolation of the intervention effect.

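### The allowance for 25% loss multiplies by 1.25 where it should divide by 0.75, so 197 per group misses the plan's own completer requirement; the 90% power also makes no allowance for few randomised units

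*Protocol*

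**What the plan says.** The Sample size section of the protocol plans for "a relevant post-intervention average difference of 10 points on a 100-point evaluation questionnaire between groups" with "a standard deviation of 0.5 [31"]. It continues: "Assuming an alpha error of 0.05 and a beta error of 0.10, 84 subjects are required for each group". It then assumes 30 residents per teaching unit on average and an ICC of 0.03, taken from a cited range of 0 to 0.052, which gives a design effect of 1.87. It ends: "expecting a 25 % loss to follow-up after a 6-month period, the required sample size is 394 (197 per group"). The Abstract repeats the result: "The sample size will be 394 residents (197 in each group").

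The section does not print the formula used for the loss and gives no number of teaching units. The Randomization section makes the teaching unit the unit of allocation and aims at equal numbers of centres: "in both the intervention and control groups, the option of balanced groups will be chosen". The Discussion justifies cluster allocation "under the assumption that the number of clusters will be sufficient for each group".

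The Variables section makes the 1-month score primary and the 6-month score secondary, and the Discussion also treats 1 month as the primary measurement. The Abstract and the Objectives attach the primary objective or outcome to both 1 and 6 months.

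**The concern.** If a fraction L of those recruited is lost, recruiting n leaves n × (1 − L). To end with a required number, one divides by (1 − L). Multiplying by (1 + L) always falls short, and at 25% the gap is no longer a rounding matter. Because 197 is called the required size, the document states a target that fails its own condition, and the Abstract repeats it.

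The second part concerns what the design effect does not do. It inflates the variance for clustering but keeps the normal critical value of 1.96, as if the between-unit variance were known. With a small number of randomised units that variance is estimated from few of them, and the critical value should come from a t distribution with about 2k − 2 degrees of freedom for k units per arm. The protocol assumes that the number of units will suffice without giving or checking it.

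At stake is whether the 90% power attached to 394 residents can be taken at face value by those who recruit units and by those who later read a null result.

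**Working it through.** **Inputs (Sample size section).** Difference 10 points; alpha 0.05; power 0.90; 30 residents per unit; ICC 0.03, cited upper value 0.052; loss 25% by 6 months.

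**Two readings needed to reproduce the plan.** A standard deviation of 0.5 points cannot be meant: with a 10-point difference it would need 1 resident per group. Read as a standardised effect d = 0.5 (SD 20 points), it gives the plan's figure. Sidedness is not stated. Two-sided is assumed because one-sided would give 69 and because the Statistical analysis section plans a Student's t test "with a 95 % CI will be performed to compare both groups' results".

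**Reproducing 197.**
- Unadjusted: 2 × ((1.960 + 1.282)/0.5)² = 84.06; the plan states 84.
- Design effect: 1 + (30 − 1) × 0.03 = 1.87.
- Required after loss: 84 × 1.87 = 157.08.
- Loss by multiplication: 157.08 × 1.25 = 196.35, rounded up to **197**. This matches.
- Loss by division: 157.08 / 0.75 = 209.44, rounded up to **210** (420 in total). This does not match.
- Check: 197 × 0.75 = 147.75, which is 9.33 short of 157.08. The loss that 197 can bear is 1 − 157.08/197 = 20.3%.

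**Power of 197 per group after 25% loss, normal approximation.** Effective n = analysed n / design effect; noncentrality = 0.5 × √(effective n / 2); power = Φ(noncentrality − 1.96).
- Design effect held at 1.87: 147.75/1.87 = 79.0; noncentrality 3.143; power about 88%.
- Loss spread evenly, so that units fall to 30 × 0.75 = 22.5: design effect 1 + 21.5 × 0.03 = 1.645; 147.75/1.645 = 89.8; noncentrality 3.351; power 91.8%.

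**Allowing for the number of units.** 197/30 = 6.6, so about 7 units per arm and 2 × 7 − 2 = 12 degrees of freedom (critical value 2.179). Power is from the noncentral t with the same noncentrality. In each pair of figures, the first holds the design effect at its 30-resident value and the second uses 22.5 residents per unit.

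| Recruited per group, 25% loss | ICC | Normal approximation | t, 12 df |
|---|---|---|---|
| 197 | 0.03 | 88% / 91.8% | 82.2% / 86.7% |
| 210 (7 units of 30) | 0.03 | 90.1% / 93.3% | 84.5% / 88.7% |
| 197 | 0.052 | 77% / 84.0% | 70.3% / 77.4% |

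**Smaller loss, 197 per group, ICC 0.03, t on 12 df, units shrinking with the loss.** No loss: 91.4%. 5% loss: 90.7% (90.0% with the design effect held at 1.87). 10% loss: 89.9%.

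**More, smaller units, 197 per group, 25% loss, ICC 0.03, units shrinking with the loss.** 25 residents per unit (8 units per arm): 89.7%. 20 per unit (10 units): 92.6%. 15 per unit (14 units): 95.1%.

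**The case against.** The inflation error cannot be argued away on the stated inputs, but a good deal can be said against making much of it.

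- **The slip alone costs little.** The 88% figure pairs 147.75 completers with a design effect for 30 analysed residents per unit. If a quarter are lost, units are smaller and the design effect falls to 1.645, which takes the normal-approximation power above 90%. This stands.
- **The loss belongs to 6 months.** The primary outcome is at 1 month, and the protocol gives no loss for that visit. With about 5% or less, 197 per group keeps about 90–91% even on 12 degrees of freedom. This stands, though the section sizes the trial on the 25%, and the Abstract and Objectives tie the primary evaluation to 6 months as well.
- **The number of units is not fixed.** All Spanish teaching units are invited, 30 is only an average, and no 12-df test is named. More and smaller units would raise power. This stands too: the few-units figures are conditional on 30 per unit. It is also the reason to state the number.
- **The choice of degrees of freedom is analysis-plan detail.** That is true of the analysis. The power claim, however, is made in the protocol and rests on the number of units.

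A reader might infer that 197 per group cannot deliver 90% power. The documents do not support this as a flat statement, for the first three reasons. Nor is 6.6 units per arm an error in itself: an average unit size need not divide the total, and balanced allocation fixes equal numbers of centres, not 30 residents in each.

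**Conclusion.** The arithmetic error is certain on the plan's own inputs: 210 per group, not 197, is needed to keep 157.08 after 25% loss, a shortfall of 13 per group or 26 in total. Its effect on power is minor, at most about 2 points, and nil if the smaller analysed units are credited.

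The lack of any allowance for few units matters more, but it is conditional. With units of 30 (about 7 per arm), 25% loss and ICC 0.03, power is about 82–87% for 197 per group and 85–89% for 210. At the cited upper ICC of 0.052 it is about 70–77% for 197. Correcting to 210 therefore meets the plan's own method but does not bring the t-based power to 90% under these assumptions.

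All power figures rest on d = 0.5, a two-sided 5% test and, unless stated otherwise, the 6-month loss. They do not show that the 1-month primary comparison is underpowered.

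**What to change.** In the Sample size section and the Abstract, do one of the following:

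- correct the figure to 210 per group (420 in total); or
- keep 394 and restate the tolerated loss as about 20% (197 × 0.80 = 157.6, which covers 157.08); or
- keep 394 and 25% loss, and restate the power as about 88% with the design effect at 1.87.

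In either case, state the assumed number of teaching units per arm and the loss expected at 1 month as well as at 6 months. Report power from a cluster formula with t degrees of freedom, with the result at ICC 0.052 beside it, in place of the flat 90%. Reword the standard deviation of 0.5 as a standardised difference, or give the SD in points.

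Keeping 394 costs a few sentences and no recruitment. Correcting to 210 adds 26 residents in total. If 90% on the t basis is wanted at 25% loss with units of 30, 8 units per arm (240 per group) give about 90–93% at ICC 0.03; that is a design choice, and the correction does not depend on it.
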